## Abstract

**Background:**

Among adults in the United States, asthma prevalence is disproportionately high among African American women; this group also experiences the highest levels of asthma-linked mortality and asthma-related health care utilization. Factors linked to biological sex (e.g., hormonal fluctuations), gender roles (e.g., exposure to certain triggers) and race (e.g., inadequate access to care) all contribute to the excess asthma burden in this group, and also shape the context within which African American women manage their condition. No prior interventions for improving asthma self-management have specifically targeted this vulnerable group of asthma patients. The current study aims to evaluate the efficacy of a culturally- and gender-relevant asthma-management intervention among African American women.

**Methods/Design:**

A randomized controlled trial will be used to compare a five-session asthma-management intervention with usual care. This intervention is delivered over the telephone by a trained health educator. Intervention content is informed by the principles of self-regulation for disease management, and all program activities and materials are designed to be responsive to the specific needs of African American women. We will recruit 420 female participants who self-identify as African American, and who have seen a clinician for persistent asthma in the last year. Half of these will receive the intervention. The primary outcomes, upon which the target sample size is based, are number of asthma-related emergency department visits and overnight hospitalizations in the last 12 months. We will also assess the effect of the intervention on asthma symptoms and asthma-related quality of life. Data will be collected via telephone survey and medical record review at baseline, and 12 and 24 months from baseline.

**Discussion:**

We seek to decrease asthma-related health care utilization and improve asthma-related quality of life in African American women with asthma, by offering them a culturally- and gender-relevant program to enhance asthma management. The results of this study will provide important information about the feasibility and value of this program in helping to address persistent racial and gender disparities in asthma outcomes.

**Trial Registration:**

ClinicalTrials.gov: NCT01117805

## Background

### Asthma and asthma-management among African-American women

Asthma prevalence in the United States continues to be at a worrying high level across the population, and both women and African Americans continue to be disproportionately affected by this illness. Among adults, prevalence among women is nearly double that among men (9.7 vs. 5.5%), representing a shift from childhood where asthma predominates among boys, and is higher among non-Hispanic Blacks compared to non-Hispanic Whites (8.7 vs. 8.1%) [1]. Gender and race disparities are also present in measures of asthma morbidity, emergency department use/hospitalization, and mortality [2-4].

The greater asthma incidence, prevalence and severity observed among women compared to men has been related to multiple issues; for example, hormonally-linked biological differences [5] and greater effects of smoking and obesity [5,6]. Certain risk factors for poor asthma outcomes such as depression and medication non-adherence may also be more common among women [6]. Similarly, multiple factors, many of which are associated with low socioeconomic status (SES), likely play a role in the greater asthma burden among African Americans; e.g., lack of access to optimal medical care, greater prevalence of indoor and outdoor environmental triggers commonly found in low-income areas, lack of asthma education and support, racial discrimination, and less use of anti-inflammatory medicines [7-10].

With excess risk conferred by both gender and race, African American women comprise a particularly vulnerable group of asthma patients, and are thus a logical focus of programs to improve asthma outcomes. The design of these programs should consider factors linked to both sex/gender and race that may affect asthma management. For example, many women experience menstruation-linked fluctuation in asthma symptoms and have greater exposure than men to common asthma triggers such as household cleaning products [11]. Compared to other ethnic groups, African American women have a higher average body mass index (BMI), which has been linked to more severe asthma symptoms [12]. In addition, among women screened for participation in a birth cohort study, African American women had higher levels of total IgE, with specific sensitivity to more aeroallergens, than their Caucasian counterparts [13]. They may also have a greater reliance on over-the-counter or home remedies and be more likely to delay care-seeking [14].

### Adapting *Women Breathe Free *for an African American population

A telephone-based asthma education intervention for women age 18 and over, *Women Breathe Free*, was the first published trial of an intervention addressing sex and gender-role issues in asthma management. This intervention was efficacious in reducing health care utilization while improving asthma-related quality of life and clinical status [15,16]. However, unpublished analyses examining the subgroup of African American women in this trial (n = 89) suggest that this group failed to achieve the same magnitude of positive outcomes as the overall study population, although statistical power was limited. These findings suggest the possibility that an intervention that better meets the specific asthma-education and support needs of African American women may achieve more positive results. There are few examples in the literature of asthma-management programs relevant to the needs of African American patients (see [17] for review), and none that are specific to women.

The *Women Breathe Free *program was adapted to meet the needs and preferences of African American women using a process that consisted of two primary phases: focus groups and expert review. In the first phase, forty-four African American women with asthma who had completed the *Women Breathe Free *study were recruited to take part in focus group discussions. Open-ended questions were posed about asthma-management concerns, and also the social, cultural, clinical, and practical aspects of an intervention that would help them better manage their asthma. Major themes that emerged from these groups included: difficulties associated with being overweight; extensive family care responsibilities; costs associated with asthma care and medicines as a barrier to management; the influence of social network members on asthma management; and the importance of social support. Desired characteristics of an asthma-education program included: a personalized program that addresses asthma-management challenges in the context of economic constraints; counselors who share the women's cultural background and demonstrate respect for their social and cultural experience, values, and beliefs; counselors who are knowledgeable, patient, and able to motivate and offer 'hand holding' when needed; delivered by telephone, a mode which the women found more flexible, personal, and private than group meetings; and materials that make use of checklists and graphics in place of extensive text.

After materials related to intervention content and process were initially developed based on focus group results, the second phase of adaptation, expert review, took place. A panel was convened consisting of three doctoral-level experts in asthma and cultural appropriateness (an epidemiologist/health educator, a cultural anthropologist, and a social worker). All panel members were themselves African American women who had extensive experience working in the field of asthma education in the African American community. This group reviewed all materials and made suggestions for modifications as needed. A summary of the ways in which the new program, called *Women of Color and Asthma Control (WCAC)*, is designed to be relevant to an African American population can be found in Table 1.

**Table 1 T1:** Examples of culturally-relevant aspects of the *Women of Color and Asthma Control *intervention

Program element	Relevance
Program staff	Intervention counselors are African-American women, to enhance rapport with participants. Non-counseling staff are trained in issues related to cultural sensitivity.

Participant visuals	Photographs in workbook represent a diversity of African American women and families. Photos of telephone counselors included in workbook.

Workbook content	Use of culturally-relevant activities when discussing potential triggers (e.g., nail salons, church and family gatherings). Use of culturally-relevant examples in list of potential asthma-management problems (e.g., asthma medicine is expensive so I only buy it when my symptoms are bad, my family thinks prayer is all I need to take care of my asthma).

Telephone session content	Culturally-linked factors addressed by telephone counselors during program sessions, where relevant: --Potential perception that asthma is life-threatening and that fears, if not managed, can block effective action. --The role that being overweight may play in worsening asthma symptoms. --Impact of time and family responsibilities, including extended family. --Economic constraints in managing asthma. --The importance of community life and the potential influence on asthma management of the beliefs of other women in their social circles. --Potential use of alternative therapies. --Possibility of frequent asthma symptoms. --Possibility of use of urgent and emergency services for asthma as a regular feature of care. --Possibility of not using anti-inflammatory medicine. --Generation of a potential allergy profile to help in formulating strategies related to environmental control, potential seasons of increased risk, and the relationship between asthma and rhinitis. -Effective communication with health care team and other sources of support.

## Methods/Design

This study uses a randomized controlled design (intervention vs. usual care) to test the efficacy of *Women of Color and Asthma Control*, a telephone-based asthma management intervention for African American women. All study procedures have been reviewed and approved by the Institutional Review Board at the University of Michigan (IRB Study HUM00033784).

### Study hypotheses

Compared to women in the usual care group, women in the intervention group will: 1) use emergency department (ED) services for asthma less frequently and be hospitalized for asthma less frequently; 2) need urgent care in a physician's office less often; 3) experience fewer symptoms of asthma; and 4) have higher levels of asthma-related quality of life. We expect to see between-group differences at both 12 and 24 months from baseline.

### Sample size determination

The sample size of 420 at baseline (210 women in each treatment condition) was determined by power calculations using the primary study outcomes of ED visits and hospitalizations in the last 12 months, taking into account 30% attrition rate over 24 months and a loss of 5 women per group due to pregnancy. In previous work we observed that for ED visits and hospitalizations the treatment takes at least 12 months to reach full effect; thus, the sample size calculations for these outcomes were performed at 24 months. However, for the other outcomes, e.g. asthma symptoms and QOL, the intervention effect occurred during the first 12 months and the power calculations for these were performed at 12 months, which is the same or more conservative than 24 months.

The relatively rare occurrence of ED vists and hospitalizations for asthma requires a large sample size to detect clinical improvement over time. In previous work by the authors based on 364 participants with asthma, belonging to the intervention group was associated with a 75% reduction for hospitalization and 53% for ED visits with at least 80% power (alpha = 5%) at 24-month follow-up. We conservatively estimate a smaller reduction for the same two outcomes with a similar sample size and the same statistical power. An initial total sample of 420 and a final available sample of 286 will have sufficient power to detect a 32% improvement in the proportion of participants having at least 1 ED visit (42% in mean ED visits) and a 41% improvement in the proportion having at least one hospitalization (46% in mean hospitalizations). Note that these power calculations also ensure our ability to assess other important outcomes such as asthma symptoms and asthma quality of life.

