### Participant recruitment

We are recruiting a total of 420 participants for this study over an approximately two-year period. To be eligible, participants must: 1) be a woman 18 years of age or older and self-identify as African American, 2) have access to a landline or mobile telephone, 3) not be pregnant, and 4) not reside in an institution.

Primary recruitment is through the University of Michigan Health System (UMHS), with eligibility requirements for participants including: 1) have at least one outpatient visit at the University of Michigan Health System (UMHS) in the past year; and 2) be listed on the UMHS Asthma Patient Registry, a validated all-payer registry of patients with persistent asthma cared for within UMHS. Lists of potential participants from the UMHS Asthma Registry are periodically generated and reviewed by a research nurse. Eligible patients are then mailed a packet including consent forms, a study overview page and a letter from the project director inviting them to enroll. The letter is followed by a recruitment phone call, which includes information about the study's purpose, randomization, and data collection. Upon returning a signed consent form, participants are enrolled in the study and randomized after baseline data collection.

Secondary recruitment methods include posting on the University of Michigan's clinical trial research database, http://UMClinicalStudies.org; partnering with the Blue Cross Blue Shield of Michigan (BCBSM) to identify members in the area who meet study criteria; and instituting a community recruitment plan that includes posting flyers in local health centers, hair salons, community organizations, and churches. All patients recruited outside of the Registry will have patient records in the UMHS or BCBSM systems that can be used for analysis of outcomes related to health care utilization. Any potential participant contacting study staff after learning about the study through one of these secondary recruitment methods will be screened for eligibility and then mailed the study packet as described above.

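### The detectable effects stated for 286 women presuppose usual-care event proportions of about 51% (ED) and 37% (hospitalization) under a standard test, which is hard to reconcile with calling these events relatively rare

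*Protocol article*

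**What the plan says.** All the sample size statements stand in the protocol article under Sample size determination. The trial starts with 210 women per arm, "taking into account 30% attrition rate over 24 months and a loss of 5 women per group due to pregnancy". The calculation for the two primary outcomes, ED visits and hospitalizations in the last 12 months, is placed at 24 months.

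The second paragraph of that section opens: "The relatively rare occurrence of ED vists and hospitalizations for asthma requires a large sample size". It then cites the authors' earlier work in 364 participants, with a 75% reduction for hospitalization and 53% for ED visits "with at least 80% power (alpha = 5%) at 24-month follow-up". It continues: "We conservatively estimate a smaller reduction for the same two outcomes with a similar sample size and the same statistical power". The resulting claim is: "An initial total sample of 420 and a final available sample of 286 will have sufficient power to detect a 32% improvement" in the proportion with at least one ED visit (42% in the mean), and a 41% improvement in the proportion with at least one hospitalization (46% in the mean).

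The article gives no usual-care proportion or mean, no test and no sidedness. Under Participant recruitment, women from the main source must "have at least one outpatient visit at the University of Michigan Health System (UMHS) in the past year" and be listed on a registry of patients with persistent asthma. A previous ED visit or admission is not listed as a requirement.

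**The concern.** For a comparison of two proportions, the number per arm, the significance level, the power and the relative reduction together fix the control proportion. The article states all of these except sidedness, so the usual-care rate behind its claim can be recovered approximately. The recovered rates are high: about half of usual-care women visiting an ED for asthma within a year, and more than a third being admitted. The paragraph that makes the power claim also gives the rarity of these events as the reason for needing a large sample.

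Both outcomes are primary. If the true rates are well below the implied ones, the trial could miss reductions of the size it names more often than a reader would expect, and a null result would be taken as stronger evidence against the program than it is.

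**Working it through.** **Inputs.** From Sample size determination: 210 per arm; 5 per arm lost to pregnancy; 30% attrition; 286 available at the end; 5% significance level and 80% power (given for the earlier work and carried forward as the same power); reductions of 32% and 41%. My assumptions: improvement means a between-arm relative reduction in the proportion, and the test is an unadjusted two-sided comparison at 24 months. The article states neither.

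**Step 1, the plan's own figure.** (210 − 5) × 0.70 = 143.5, taken as 143 per arm and 286 in total. This reproduces.

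**Step 2, the implied usual-care proportion.** With p1 the usual-care proportion, p2 = p1(1 − r) and p̄ = (p1 + p2)/2,

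power = Φ{ [√n (p1 − p2) − 1.96 √(2p̄(1 − p̄))] / √(p1(1 − p1) + p2(1 − p2)) }.

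I solved for p1 at n = 143 and power 0.80.

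- ED visits, r = 0.32: p1 = 0.510, p2 = 0.347. Check: √143 × 0.1633 = 1.953; (1.953 − 1.96 × 0.700)/0.690 = 0.84; Φ = 0.80.
- Hospitalization, r = 0.41: p1 = 0.365, p2 = 0.216. Check: √143 × 0.1498 = 1.791; (1.791 − 1.96 × 0.642)/0.633 = 0.84; Φ = 0.80.

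**Step 3, how far this depends on the assumed test.**

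| Calculation at 143 per arm | ED visits | Hospitalization |
|---|---|---|
| Two-sided, pooled variance | 51% | 37% |
| Other two-sided versions (arcsine, unpooled, log risk ratio, continuity-corrected) | 50–53% | 36–39% |
| One-sided 5% | 44% | 31% |
| Baseline-adjusted, assumed correlation 0.5 (n/0.75 = 191) | 43% | 30% |
| Baseline-adjusted, assumed correlation 0.7 (n/0.51 = 280) | 33% | 22% |

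If the improvement were a reduction in odds, 80% power would not be reached at any rate (maximum 37% for ED visits and 60% for hospitalization).

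**Step 4, power at lower rates.** These rates are illustrations; the article gives none. Two-sided 5%, 143 per arm:

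| Usual-care proportion | Power, 32% ED reduction | Power, 41% hospitalization reduction |
|---|---|---|
| 15% | 23% | 36% |
| 20% | 30% | 47% |
| 30% | 46% | 69% |
| 40% | 63% | 85% |

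**Step 5, the reduction detectable with 80% power** on the same test: 46% at a usual-care rate of 30%, 58% at 20%, and 66% at 15%.

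**The case against.** **The calculation may be coherent, with an input left unprinted.** The article gives each effect both as a proportion and as a mean. Under a Poisson model (an assumption), a 42% drop in the mean equals a 32% drop in the proportion when about 57% of usual-care women have an event. The hospitalization pair, 46% and 41%, matches at about 33%. These are close to the back-solved 51% and 37%. So high design rates were probably used, and the inputs may be in the full protocol, which is not shown. This stands as evidence that there is no arithmetic slip. It does not remove the tension, because it points to rates that the paragraph's wording does not suggest.

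**High rates are plausible here.** The women come largely from a registry of persistent asthma, the Abstract says this group has the highest asthma-related utilization, and Table 1 anticipates regular use of emergency services. This is fair, and it is why a shortfall cannot be asserted. Relatively rare is also a qualitative phrase, so no figure in the article contradicts another. The poor fit is clearer for ED visits than for hospitalization.

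**The analysis uses repeated measures.** The Analysis section plans GEE over three time points. Averaging both follow-ups with baseline adjustment would lower the implied rates to about 30–35% and 19–24%, at assumed correlations of 0.3 to 0.6. But the article places the calculation for these outcomes at 24 months, so that is not the calculation it describes. Baseline adjustment remains possible and is included in the range above.

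**Stronger readings that the article does not support.** A reader might infer that the stated power is not delivered. That does not follow, because the true usual-care rates are unknown. A reader might also try to derive those rates from the earlier work's effects and sample. The article says that work had at least 80% power, so this gives only lower bounds. Nor are the words conservatively and similar sample size shown to be wrong: the assumed reductions are smaller than those reported before, and 420 enrolled is fairly similar to 364.

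**Conclusion.** The point holds in a limited form. The article's sample size, effects, power and description of event frequency do not sit together under a standard two-proportion test at 24 months. The stated power presupposes usual-care proportions of about 51% for ED visits and 37% for hospitalization. Allowing for a one-sided test, or for baseline adjustment at correlations up to 0.7, it still presupposes at least about 33% and 22%. The power claim is therefore not supported by the document's own description of the events. This is more than an unprinted input, because the article makes the power claim and the rarity statement side by side. Whether power is in fact below 80%, and by how much, is conditional on rates that the article does not give. The conclusion also assumes that improvement means a between-arm relative reduction.

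**What to change.** Using the 12-month histories collected at baseline before randomization, tabulate the proportion with at least one event and the mean number of events for each primary outcome, pooled and blinded to arm. State these rates together with the test, its sidedness and any gain assumed from baseline adjustment. Then restate either the reductions detectable with 80% power, or the power for 32% and 41%, at 143 per arm over a range of rates around the estimates. Reconcile the rarity wording with the rates found, or remove it.

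The cost is one blinded tabulation and a revised paragraph, with no extra participants and no effect on the type I error rate. The downside is that the stated detectable effect may become less favourable.

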### Participant recruitment

We are recruiting a total of 420 participants for this study over an approximately two-year period. To be eligible, participants must: 1) be a woman 18 years of age or older and self-identify as African American, 2) have access to a landline or mobile telephone, 3) not be pregnant, and 4) not reside in an institution.

Primary recruitment is through the University of Michigan Health System (UMHS), with eligibility requirements for participants including: 1) have at least one outpatient visit at the University of Michigan Health System (UMHS) in the past year; and 2) be listed on the UMHS Asthma Patient Registry, a validated all-payer registry of patients with persistent asthma cared for within UMHS. Lists of potential participants from the UMHS Asthma Registry are periodically generated and reviewed by a research nurse. Eligible patients are then mailed a packet including consent forms, a study overview page and a letter from the project director inviting them to enroll. The letter is followed by a recruitment phone call, which includes information about the study's purpose, randomization, and data collection. Upon returning a signed consent form, participants are enrolled in the study and randomized after baseline data collection.

Secondary recruitment methods include posting on the University of Michigan's clinical trial research database, http://UMClinicalStudies.org; partnering with the Blue Cross Blue Shield of Michigan (BCBSM) to identify members in the area who meet study criteria; and instituting a community recruitment plan that includes posting flyers in local health centers, hair salons, community organizations, and churches. All patients recruited outside of the Registry will have patient records in the UMHS or BCBSM systems that can be used for analysis of outcomes related to health care utilization. Any potential participant contacting study staff after learning about the study through one of these secondary recruitment methods will be screened for eligibility and then mailed the study packet as described above.

To enhance recruitment and retention of participants, a number of strategies are employed. Strategies include: 1) providing a $20 gift card upon completion of each data-collection interview; 2) mailing periodic greeting cards to establish a personal connection; 3) providing each intervention-group participant with her counselor's photograph and a personalized letter; 4) utilizing as recruiters, interviewers, and counselors individuals who share a cultural understanding and who have worked with and in the African American population; and 5) attempting contacts over a period of several weeks since disconnected phone lines are sometimes reconnected after a period of time.

